## Methods/design

The AmbOx study is a UK, multicentre, prospective, randomised controlled crossover trial of ambulatory oxygen against no ambulatory oxygen over a 4-week period (2 weeks on ambulatory oxygen and 2 weeks on no portable oxygen), to evaluate the effects of ambulatory oxygen on health status in patients with ILD. Patients whose SaO_2_ at rest is ≥94% will be screened by performing a 6MWT as part of their routine clinical assessment in order to identify those patients whose SaO_2_ drops to ≤88%. In those who desaturate below this threshold, a further 6MWT will be conducted with titration of oxygen flow so that for least half of the 6MWT, oxygen saturation with supplemental oxygen is maintained at >90% (for more detailed information on oxygen titration, see section 10.2 of the protocol (Additional file 1).

Following consent to the study, patients meeting eligibility criteria and deemed clinically stable at the end of the 2-week run-in period, and not expecting to require any change in their background medication, will be assigned in random order to 2 weeks on ambulatory oxygen or no oxygen during the baseline visit. Optimal oxygen flow rates will be determined during the screening visit on the basis of the entry 6MWT on oxygen, as detailed above. At the start of the active part of the trial, the effects of ambulatory oxygen on 6MWT performance will be formally evaluated by performing two 6MWTs, one on oxygen and one on placebo air-filled canisters, at the flow rate identified during the screening visit, in random order, with a rest of at least 30 min between tests. The patient will be blind to the content of the canisters. Measured parameters will include 6MWT distance, oxygen saturation and heart rate measured continuously (WristOx2™ model 3150), Borg Dyspnoea and Fatigue Score [21] before and at the end of the test, time to recovery of heart rate, and oxygen saturation. These parameters will be related to changes in the primary and secondary outcome variables as detailed in subsequent sections, to identify any baseline predictors of responsiveness. Two different randomisation lists, independent of each other, will, therefore, be used. One randomisation list will determine the order of placebo air versus oxygen-filled canisters for the placebo-controlled 6MWT occurring at the baseline visit, the other randomisation list will determine the order of oxygen versus no intervention for the 4-week trial.

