### Assignment of interventions

Randomisation allocation as to the order of treatment will be released using an interactive web-based randomisation system (InForm), set up by Imperial College Clinical Trials Unit (ICTU). Simple, block-method randomisation will be performed to determine the order of treatment.

All study patients will be randomised during baseline visit as follows:Randomisation as to the order in which subjects will perform the 6MWT on oxygen versus air. The patients will be blind to the content of the canistersRandomisation as to the order in which subjects will have the portable home oxygen versus no oxygen during the first 2 weeks of treatment

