### Primary outcome measure

The primary outcome will be the difference in K-BILD score on oxygen compared to no oxygen. We will use a generalised linear model with the difference in health status as the independent variable and treatment sequence as a covariate. If the assumption of the mixed model is not met, data will be either log-transformed and/or other nonparametric methods will be considered. Any adjusted analyses will be performed as secondary sensitivity analysis including adjusting for any covariate that is itself linked to the primary outcome (see below)Analysis of the primary outcome will be by intention-to-treat. The data will be analysed according to the initial randomisation groups irrespective of subsequent withdrawals. However, should there be a sizeable frequency of protocol variation, per protocol analysis will also be performedThe hypothesis to be tested is that ambulatory oxygen improves health status compared to no treatment. The study will be considered positive if statistical significance at the level of 0.05 (two-tailed) is achievedo Sensitivity analyses will include adjustment for any covariates linked to the primary outcome. These may include baseline K-BILD measurement, age, gender, smoking history, Body Mass Index (BMI), ILD severity as measured by the Composite Physiologic Index (CPI), presence of PH as measured by echo, baseline BNP levels, etc.o Patient-reported consumption of oxygen cylinders will also be factored in as a covariate. Its validity will be checked against oxygen company-reported cylinder consumption wherever possible, and, in a subgroup of patients, by direct observation by clinical nurse specialist (CNS) home visits (Aintree centre)o To assess the relationship between the response to supplemental oxygen measured with a series of parameters during the placebo air versus oxygen 6MWT and the benefit seen in day-to-day life with ambulatory oxygen, to identify any baseline predictors of responsiveness. These parameters will be included in the statistical model as fixed- effect variables. Possible 6MWT predictors to be analysed will include area under the curve of oxygen saturation, walked distance, maximum/minimum and mean heart rate, end-test dyspnoea, end-test oxygen saturation, end-test heart rate, and recovery times to baseline dyspnoea, heart rate and saturationo Exploratory sensitivity analyses of the effects of ambulatory oxygen will be conducted in predefined subgroups, including:

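### The model relating 6MWT response to daily-life benefit names no term for the randomised order of the two baseline walks; adding that order is a nearly free improvement

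*Protocol article*

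**What the plan says.** Methods/design describes the baseline walks as "one on oxygen and one on placebo air-filled canisters, at the flow rate identified during the screening visit, in random order", and asks for a pause of 30 minutes or more before the second walk. It then states that "Two different randomisation lists, independent of each other, will, therefore, be used", and that "One randomisation list will determine the order of placebo air versus oxygen-filled canisters for the placebo-controlled 6MWT"; the other list sets the order of the two home periods. Assignment of interventions repeats the first of these as a separate step: "Randomisation as to the order in which subjects will perform the 6MWT on oxygen versus air".

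In the Statistical analysis part, Primary outcome measure, the main model has the "difference in health status as the independent variable and treatment sequence as a covariate". (The K-BILD difference is called the independent variable there but is plainly the outcome.) The same section sets out the predictor analysis. It relates the response to oxygen on the air-versus-oxygen walks to benefit in daily life, lists candidate 6MWT parameters, and says "These parameters will be included in the statistical model" as fixed effects. Covariates for adjusted analyses are those linked to the primary outcome. Walk order appears in none of these lists.

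Explanatory outcome measures describes the 6MWT response as improvement on oxygen relative to placebo air. No section says how the per-patient value is constructed.

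**The concern.** Two walks under two conditions, in randomised order on the same day, form a two-period crossover within each patient. Randomising the order balances a fatigue or practice shift in the group mean difference. It does not remove the shift from any one patient's difference, and a predictor analysis works on individual differences.

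The home-oxygen sequence term cannot help, because the two lists are independent. The stated adjustment rule would not normally bring walk order in either: a randomised walk order has no reason to be linked to the K-BILD difference, so a rule that selects covariates linked to the outcome passes over it. Order matters here because it affects the predictor, not the outcome.

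At stake is whether the walk-test response to oxygen predicts benefit in daily life. This is a stated aim (Objectives), an additional secondary outcome and the first explanatory outcome. An unmodelled shift acts in one direction only: it weakens the apparent association.

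**Working it through.** **The plan's own figure.** The article gives no calculation for the predictor analysis. Its primary sample size reproduces: a paired t-test with difference 8, SD of the paired difference 20, two-sided 5% and 90% power needs 68 patients, and 68/(1 − 0.15) = 80. The present point does not touch that figure. I use n = 68 evaluable patients below.

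**Inputs from the article.** Two walks, randomised order, order list independent of the home sequence, sequence in the model.

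**Assumptions.** The response is the oxygen-minus-air difference; walk orders are split 1:1; the shift is the same for every patient. The sizes of s and SD are also assumed, because the article gives neither.

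**Derivation.** Let r be the order-free difference, with standard deviation SD, and let the second walk shift by s. The recorded difference is

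- D = r + s if oxygen came second,
- D = r − s if oxygen came first.

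So two patients with the same r can differ by 2s through order alone. Write D = r + s·o, with o = ±1, independent of r, of the home sequence and of the outcome. If the outcome has slope β on r, then Cov(outcome, D) = β·SD² and Var(D) = SD² + s². Hence

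- slope on D = β × SD²/(SD² + s²) = β/(1 + k²), with k = s/SD,
- correlation with D = ρ/√(1 + k²).

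Power for an assumed true correlation ρ = 0.4 comes from Fisher's z: Φ(atanh(ρ′)·√(n − 3 − c) − 1.96). Here ρ′ is the correlation with the predictor as used: ρ/√(1 + k²) without an order term and ρ with one. c counts the other covariates: 1 (home sequence) without walk order, 2 with it. For k = 0.5 without order, ρ′ = 0.4/√1.25 = 0.358, and power is Φ(0.374 × 8 − 1.96) = 0.85.

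| k = s/SD | Slope retained | Slope loss | Correlation factor | Power, order omitted | Power, order included |
|---|---|---|---|---|---|
| 0.1 | 0.99 | 1% | 0.995 | 0.92 | 0.92 |
| 0.25 | 0.94 | 6% | 0.97 | 0.91 | 0.92 |
| 0.5 | 0.80 | 20% | 0.89 | 0.85 | 0.92 |
| 0.75 | 0.64 | 36% | 0.80 | 0.76 | 0.92 |
| 1.0 | 0.50 | 50% | 0.71 | 0.64 | 0.92 |

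**In metres, for walked distance.** With an assumed SD of 30 m, shifts of 10, 20 and 30 m retain 900/1000 = 0.90, 900/1300 = 0.69 and 900/1800 = 0.50 of the slope. With SD 40 m the factors are 0.94, 0.80 and 0.64.

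**Check by simulation** (n = 68, 4,000 runs per setting). With ρ = 0.4 and order omitted, the slope retained was 0.94, 0.80 and 0.49 at k = 0.25, 0.5 and 1.0. With order included it was 1.00, 1.01 and 1.00. With no true association, the rejection rate lay between 4.8% and 5.2% in all settings, with or without the order term.

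**Cost when there is no shift.** At k = 0, power is 0.924 without order and 0.920 with it.

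**The case against.** The strongest reply is that the article does not make the choice at issue. It never says that an unadjusted difference will be used, and it neither includes nor excludes walk order. It is a condensed account that points to a full protocol. The predictors are introduced as possible ones and the covariate list is left open. A reader might infer that the plan has decided to ignore walk order; the text does not support that. What stands against the reply is that the article does state a covariate rule and does name an order term, and neither would normally lead an analyst to walk order.

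The second reply concerns size, and it is sound. Nothing in the article indicates how large the shift is. Patients have already done a screening walk and a titration walk, which limits practice effects, and the rest of at least 30 minutes limits fatigue. The lower rows of the table are therefore less plausible than the upper ones, and up to a quarter of an SD the loss is slight.

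Three further inferences would go too far:

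- That patients would be wrongly classed as responders: the article defines no 6MWT responder category.
- That a false positive could arise: omitting order leaves type I error at its nominal level.
- That the trial's main result is at risk: the primary K-BILD comparison uses no 6MWT response.

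Finally, an order term removes only the average shift. Fatigue that differs between patients stays in the predictor.

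**Conclusion.** The point holds as a minor one. As described, the predictor analysis has no term for the randomised order of the two walks, and what it does specify would not normally supply one. Any average shift between the walks would then dilute the association under study, to an extent that depends wholly on an assumed s/SD: negligible at 0.1, appreciable from about 0.5. This rests on reading the response as an oxygen-minus-air difference. If the oxygen and air values were entered separately, the formula would differ, but each value would still carry the shift. The documents do not show that the predictor analysis will fail or that order has been deliberately left out. The point is a free improvement to a secondary and explanatory analysis.

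**What to change.** State how the per-patient 6MWT response is formed. Include the randomised walk order (oxygen first or air first) as a covariate in every model that uses a 6MWT response as predictor, whether or not it is linked to the K-BILD difference, and alongside the home-oxygen sequence rather than in place of it. Report the estimated order effect for each 6MWT parameter: half the difference in mean oxygen-minus-air response between the oxygen-second and oxygen-first groups.

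The cost is one degree of freedom per model. The order is already assigned by its own list, so no new data are needed. The report should say that the adjustment removes the average shift only.

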### Secondary outcomes

Comparison of differences in secondary outcome measures on and off ambulatory oxygen treatment, will be performed by similar methods as for the primary outcome

### Qualitative interview analysis

Interviews will be transcribed verbatim, checked and anonymised. Transcripts will be analysed thematically using a framework approach [30]. NVivo 10 software (QSR International Pty Ltd., www.qsrinternational.com) will be used to manage and index the data prior to charting, mapping and interpretation. Framework analysis provides a systematic approach to analysis useful for applied qualitative research and enhances visibility of analysis for policy-makers and practitioners. Further, it is particularly useful for linking qualitative to quantitative data. This would facilitate a mixed-methods analysis of the broader dataset, thus providing comprehensiveness and greater knowledge yield [31, 32], making best use of the data collected.

### Patient public involvement: patient/carer focus group

Patients and carers living with ILD who are not participating to the study will be invited to participate to a focus group to provide patient and carer perspectives on a sample of the anonymised interview transcripts and their interpretation of the analysis.

### Interim analyses

There will be no formal interim analysis as the study duration is short, and we do not expect any significant undesirable outcomes. A regular review of safety data will be conducted to monitor the safety of patients in the trial. A Data Monitoring Committee (DMC) will follow number of deaths, early discontinuation due to AEs and SAEs in an unblinded fashion. A planned DMC meeting will be held to review all available data twice yearly.

### End of study

The final study visit will be the one at the end of the second of the 2-week study periods The trial will formally end when the final subject completes their week-4 visit.

Data from the study will be published in abstract form at international meetings and will be submitted for publication in a peer-reviewed journal and will be reported to the study funder.

## Discussion

Fibrotic lung diseases are an important cause of morbidity and mortality, with a devastating impact on quality of life. With currently available treatments providing only partial effectiveness and often, at best, stability of disease, interventions to improve day-to-day quality of life are crucial in this group of patients. This trial will be the first to prospectively assess the impact of ambulatory oxygen in patients with fibrotic ILD and to explore the outcomes for which it is most effective, the predictors of benefit and the variables/patient characteristics associated with lack of response. This study will form an essential precursor to the development of ILD-specific guidelines on ambulatory oxygen use. Ultimately, if proven to be effective and cost-effective, the appropriate prescription and use of ambulatory oxygen should lead to prolonged patient independence and mobility, allowing maintenance of fitness levels and of active roles in daily life, with increased psychological and physical wellbeing, as well as potentially reduced health-related costs.

### Trial status

Recruitment to AmbOx began in August 2014. The trial is currently actively recruiting in the UK.

## Abbreviations

ILD: Interstitial lung disease
K-BILD: King’s Brief Interstitial Lung Disease Questionnaire
SaO_2_: oxygen saturation
SGRQ: St. George’s Respiratory Questionnaire
UCSD SOBQ: San Diego Shortness of Breath Questionnaire.
